### Sample size

Sample size calculation was based on a two-step procedure due to the hierarchical data structure. In the first step, the sample size for an individual randomized study is calculated. Based on studies using the ‘empowerment in the process of psychiatric treatment of patients with affective and schizophrenia disorders (EPAS)’ scale [26], a medium effect (0.4 SD units) of the implementation intervention on the primary endpoint is expected. This effect is detectable with an error probability of 5% (alpha) and a power of 80% by a t-test for independent samples with a sample size of 2 × 100 participants (200 in total).

The second step takes the cluster structure of the data into account. We assume that each centre recruits 35 patients (m) on average. The design effect (DE) is needed for the inflation of the group sample size: DE = 1 + (m - 1) * ICC with the fixed cluster size m and the intra-cluster correlation coefficient ICC. We assume a liberal intra-class correlation coefficient of 0.02 to control for the correlation of the outcome of participants of the same centre. Thereby, the DE is 1 + (35–1) * 0.02 = 1.68, which gives a sample size of 200 × 1.68 = 336 patients. As every centre recruits 35 patients on average, 10 centres are needed for the trial. Due to the severity of the disease in the patient population, case number planning assumes that 70% of patients can be reached 6 months after t_0_, so that an oversampling to (35/0.7) 50 patients per study centre will be recruited, resulting in 10 centres * 50 patients = 500 participants (2 × 250) as the overall sample size. This 70% estimate is based on experiences at the Günzburg site from three studies conducted with similar populations [27–29].

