### Statistical methods

First, the sociodemographic and clinical characteristics will be listed. Categorical variables will be described as absolute and relative frequencies and with graphical representation (e.g., bar chart). Continuous variables will be described by means and SDs, supplemented by minimum, median, percentiles and maximum. In addition, data will be analysed graphically (e.g., boxplot). Number of missing values will be reported for all variables of interest. Cases with missing values will be compared with those with complete data with regard to characteristics relevant for study outcomes.

The primary outcome is the improvement of empowerment 6 month after t_0_ (EPAS-t_2_) compared to baseline (EPAS-t_0_). Therefore, a hierarchical linear model (mixed model approach [30, 31]) is used to model EPAS-t_2_ as outcome and intervention, baseline EPAS-t_0_, centre and centre-size as main regressors with special attention to the intervention (confirmatory). The significance level will be set to 5% for intervention. The analysis will be based on a modified intention-to-treat (modITT)-population, using all patients with an outcome at month six (EPAS-t_2_) [32], since an imputation of the primary outcome can be misleading. Data management procedures will be implemented to reduce the drop-out rates; thus, a relatively low drop-out rate is expected. To examine a possible selection bias, the baseline data of ITT and modITT populations will be compared. In case of differences, these variables will be included in the regression models to adjust for confounding. For the independent variables, mixed model approaches can handle missing data well, and thus, no multiple imputation is needed in particular. However, according to this modITT concept, multiple imputation [33] of missing data in independent variables will be conducted by fully conditional specification (FCS) to perform a sensitivity analysis.

Other possible confounders with respect to the main outcome will be investigated by adding them into the model, eventually using backward selection procedures for variable selection and multiple imputations (*see* above). These analyses will be subjected to explorative interpretation only.

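### Drop-out at six months is called low against a planned 30% loss, mixed models are wrongly credited with handling missing covariates, and no stated analysis varies the assumption about missing EPAS

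*Protocol article*

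**What the plan says.** All of this is in the protocol article.

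- **Analysis set (Statistical methods).** "The analysis will be based on a modified intention-to-treat (modITT)-population, using all patients with an outcome at month six (EPAS-t_2_) [32". The reason given is that imputing the primary outcome could mislead. The next sentence refers to procedures against loss to follow-up and concludes: "thus, a relatively low drop-out rate is expected".
- **Planned loss (Sample size).** "case number planning assumes that 70% of patients can be reached 6 months after t_0", because of the severity of illness. The figure is drawn from three studies in similar populations, and recruitment per centre is raised from 35 to 50 on its strength.
- **Model (Statistical methods).** A hierarchical linear model has EPAS at t2 as the outcome. The main regressors are intervention, EPAS at t0, centre and centre size.
- **Missing covariates (Statistical methods).** "For the independent variables, mixed model approaches can handle missing data well, and thus, no multiple imputation is needed in particular". Multiple imputation of independent variables by fully conditional specification follows as a sensitivity analysis within the modified ITT set.
- **Selection bias (Statistical methods).** Baseline data of the ITT and modified ITT sets are compared, and variables that differ enter the models. Cases with missing values are also compared with complete cases.
- **Other outcomes.** They are to be analysed in a similar way.

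**The concern.** There are three linked problems.

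First, the analysis section offers a reassurance about drop-out that the trial's own planning does not share. Someone who reads only that section would think the excluded group is small.

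Second, the sentence on mixed models assigns their missing-data property to the wrong side of the equation. It is then used as the reason not to impute covariates in the main analysis.

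Third, leaving out patients without EPAS at t2 is itself an assumption: given the covariates in the model, those lost resemble those kept. No analysis stated in the article changes that assumption.

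The trial is not blinded, and the intervention arm gets extra group sessions whose attendance the Discussion section expects to be hard to maintain. Who is lost could therefore differ by arm. If so, the confirmatory estimate would describe the patients who could be reached, and the report would not show how far the conclusion depends on that.

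**Working it through.** **1. The plan's own figures.** Inputs are from Sample size: effect 0.4 SD, alpha 5% (taken as two-sided, since sidedness is not stated), power 80%, 35 analysed patients per centre, ICC 0.02, 70% reached.
- The t-test needs 100 per arm (power 80.4%), so 200 in total. This matches "a power of 80% by a t-test for independent samples with a sample size of 2 × 100 participants (200 in total".
- Design effect = 1 + (35 − 1) × 0.02 = 1.68, and 200 × 1.68 = 336.
- 336 / 35 = 9.6, so 10 centres, and 10 × 35 = 350 analysed.
- 35 / 0.7 = 50 per centre, and 10 × 50 = 500.

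Every figure reproduces.

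**2. What the planned loss means for the analysis set.** 500 × 0.30 = 150 patients without EPAS at t2. If loss is equal in the arms, that is 75 of 250 in each. The modified ITT set then holds 350.

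**3. Whether low drop-out fits the sample size.** With an assumed loss of 10%, keeping 35 per centre would need 35 / 0.9 = 38.9, or 39 recruits. The planned 50 follows only from 30% loss. The Statistical methods section gives no rate of its own.

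**4. The mixed-model sentence.** A likelihood mixed model describes the outcome given the covariates.
- If a patient has several outcome records and some are missing, the rest still contribute, validly under missing-at-random.
- The model has no distribution for the covariates, so a record with a missing covariate drops out unless that value is imputed.
- The planned model has one outcome record per patient, EPAS at t2. A patient with t0 and t1 but no t2 contributes nothing, so the useful property is not used.
- A patient with t2 but no t0 is also lost from the main fit. If 10% of the 350 lacked EPAS at t0 (assumed), 35 more would go, leaving 315.

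**5. Possible size of bias.** Let L be the share lost in an arm, and d the mean of dropouts minus the mean of completers, in SD, after the model's adjustment. Subscripts I and C mark intervention and control. An arm's full mean is its completer mean + L × d, so

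bias (completer effect − all-patient effect) = L_C × d_C − L_I × d_I.

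The d values and the unequal losses are assumptions; the documents give none.

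| Loss I / C | d_I | d_C | Bias (SD) | Share of 0.4 SD |
|---|---|---|---|---|
| 30% / 30% | −0.4 | −0.4 | 0 | 0% |
| 30% / 30% | −0.2 | 0 | 0.3 × 0.2 = 0.06 | 15% |
| 30% / 30% | −0.4 | 0 | 0.3 × 0.4 = 0.12 | 30% |
| 30% / 30% | −0.5 | 0 | 0.3 × 0.5 = 0.15 | 38% |
| 35% / 25% | −0.4 | −0.4 | 0.14 − 0.10 = 0.04 | 10% |
| 35% / 25% | −0.4 | 0 | 0.35 × 0.4 = 0.14 | 35% |

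With the arms' roles reversed, the sign reverses.

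**6. Reach of the planned checks.** The comparison of the ITT and modified ITT sets uses baseline data only. It ignores the course after baseline, such as t1, and no comparison by arm is stated. The imputation analysis fills in independent variables among patients who already have EPAS at t2. Neither changes what is assumed about patients without it.

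**The case against.** The case on the other side is substantial, and much of it stands.

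- **The reason for the analysis set.** A reader might infer that patients are excluded because drop-out is expected to be low. The text does not say so. Its reason is that outcome imputation could mislead, and low drop-out is a supporting remark.
- **Planned mitigation.** A reader might infer that missing outcomes are never looked at. That is wrong. The baseline comparison is there to examine selection, variables that differ are added, reasons for drop-out are recorded where possible, and patients who do not follow the intervention schedule are still interviewed. If missingness depends only on arm and the included covariates, the adjusted complete-case model can be valid. What remains is that none of this tests a departure from that condition.
- **Caution in planning.** One can plan on 70% and hope for better. But the 70% is argued from experience, and the text gives no number for the better expectation, so the passages still need reconciling.
- **Small practical effect of the covariate sentence.** Intervention, centre and centre size are known for everyone, so among the main regressors only EPAS at t0 can be missing, and covariate imputation is already a sensitivity analysis. The sentence is wrong, but its cost is limited.
- **The SAP.** Outcome sensitivity analyses are commonly left to an SAP, which is not shown. Their absence alone would be no finding. The drop-out statement and the mixed-model sentence are in this text whatever the SAP holds.
- **Replacing the primary model.** A reader might conclude that the primary analysis must become a longitudinal model with baselines constrained equal. The documents do not support that. t1 falls two weeks after both group sessions in one arm and six weeks after t0 in the other. With ten randomised centres and unblinded recruitment, equal baseline means are not assured.

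**Conclusion.** The point holds in a limited form. The drop-out statement conflicts with the planned and justified 30% loss (150 of 500). The sentence on mixed models and independent variables is technically wrong as written. The stated checks leave the assumption about missing EPAS at t2 unvaried.

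Bias is possible, not shown. It is zero with equal loss and equal gaps, and 0.04 to 0.15 SD (10% to 38% of the 0.4 SD target) in the non-zero scenarios above, all of which rest on assumed gaps.

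A reader might also infer that the sample size is at fault. It is not: 350 completers are planned against the 336 required by the protocol's formula. The issue is consistency and possible bias, not N.

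**What to change.** 1. Reconcile the remark on low drop-out with the planned 30% loss, by giving a figure and its basis or by removing the remark.
2. Delete the sentence on independent variables. Impute missing baseline EPAS and other covariates in the main analysis.
3. Keep the modified ITT covariate-adjusted model as primary if preferred, but add a sensitivity analysis in all enrolled patients. Two options would serve:
   - multilevel multiple imputation of EPAS at t2, done separately by arm, from baseline variables and EPAS at t1 if collected (Table 1 is not shown), with arm-specific delta shifts; or
   - a longitudinal mixed model with arm-by-visit terms and no equal-baseline constraint, allowing for the different timing of t1 in the two arms.

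The cost is some extra analysis work. No new data are needed for imputation from baseline variables; use of t1 depends on EPAS having been collected then. Both options start from missing-at-random, which the delta shifts then probe.

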### Interventions

In centres randomised to the experimental group, the patient guideline ‘psychosocial interventions in severe mental disorders’ will be implemented using a multimodal strategy. The core component will be a two-part group session for patients of more than 60-min duration in which the contents of the patient guideline will be clearly presented (e.g., with case examples). The group session will be carried out jointly by the study staff (e.g., a psychologist) and a peer tutor (person with a lived experience of mental illness). The group sessions will also pay attention to the availability of psychosocial interventions in the regions but will not be limited to regional offers. In addition, questionnaires and decision aids on the basis of the patient guideline will be developed to assist patients in their discussions with practitioners and to promote their active demand for suitable psychosocial therapies. Training for the use of the questionnaires and decision aids will be provided in group sessions. Individual reminders will be developed. The two-part group sessions will be offered weekly in the inpatient and day hospital setting. Participation in both parts of the event will be supported by written information flyers. Repeated participation is possible, but study participants should attend both parts at least once. Furthermore, participants will receive the patient guideline as a printed book. Essential contents of the patient guideline will be made available on the Internet and will be optimized for mobile use (www.thera-part.de). The group sessions will include a brief introduction on how to use ‘TheraPart’. The plain language materials will be developed or tested with the participation of representatives of patients and relatives. A on-part information event for relatives will occur parallel to the two-part group events for the patients.

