Patients in centres randomised to the control condition will receive treatment as usual but will be made aware of the patient guideline ‘Psychosocial interventions in severe mental disorders’ by receiving the same guideline flyers as participants in the intervention group, which summarises the key information of the guideline and refers to additional sources of information. Treatment as usual (TAU) was chosen as the control group to compare the intervention with standard treatment. Participating relatives of patients in clinics randomised to the control condition will also receive the flyer for the guideline.

Prior to the start of the study, all study staff will receive comprehensive training on the implementation of the assigned study conditions to ensure a consistent procedure across all sites. Regular retraining and supervision of the study staff will also take place. Regular exchange between all study staff and the study lead will ensure compliance with the study protocol.

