### Randomisation

The randomisation of the centres (cluster) to the intervention or control group will be done externally by the Institute for Epidemiology and Medical Biometry, Ulm University, Ulm, Germany, by a stratified block randomisation. The 10 recruiting centres will be randomised 1:1 to the intervention and control group using the size of centre (small, large) as strata. The random assignment will be performed by the randomisation program ROM [9].

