All other outcomes (*see* chapter ‘Outcomes and measurement’) will be analysed in a similar way. Subgroup analyses will be conducted separated by recruiting centres. Patient-related analyses (knowledge, attitudes, and experiences, service use, satisfaction with treatment, treatment needs and quality of life) will be conducted separately for patients with F2x and F3x diagnoses in additional subgroup analyses. Other categorisations based on quantitative variable are not planned.

Health economic evaluation (HEA) will be conducted from the societal and from the payer (statutory health insurance) perspective. Incremental cost-utility ratios (ICUR) will be computed using the differences in total (direct and indirect) costs of illness and the differences in quality-adjusted life years (QALY) between study groups over 12 months for the societal perspective. For the HEA from the payer perspective only the direct costs reimbursed by the statutory health insurance will be used as ICUR numerator. For both perspectives the stochastic uncertainty of the ICUR will be estimated by means of nonparametric bootstrapping with 2000 replications [34]. Probability of cost-effectiveness at MWTP for the gain of one QALY in the range between 0 and 100,000 € will be estimated for both perspectives by means of the cost-effectiveness acceptability curve [34]. The calculation of the QALY is based on the EQ-5D-5 L by means of the German value set [23].

All analyses will be conducted separately for patients and relatives.

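### By-centre subgroup analyses cannot show an intervention effect, because each centre is a randomised cluster and holds one arm only

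*Protocol article*

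**What the plan says.** The Randomisation section makes the centre the unit of allocation: "The randomisation of the centres (cluster) to the intervention or control group will be done externally". It continues: "The 10 recruiting centres will be randomised 1:1 to the intervention and control group using the size of centre (small, large) as strata". The Interventions section delivers each condition to whole centres. The experimental condition is described with "In centres randomised to the experimental group, the patient guideline" and the control condition with "Patients in centres randomised to the control condition will receive treatment as usual". Nowhere is a centre described as running both.

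For the primary outcome, Statistical methods specifies a hierarchical linear model of 6-month EPAS. Its regressors are intervention, baseline EPAS, centre and centre size, and intervention is the confirmatory term. All other outcomes "will be analysed in a similar way". The next sentence reads: "Subgroup analyses will be conducted separated by recruiting centres". After that, analyses of knowledge, attitudes and experiences, service use, satisfaction, needs and quality of life "will be conducted separately for patients with F2x and F3x diagnoses in additional subgroup analyses".

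**The concern.** Subgroup analysis by site makes sense when patients are randomised individually within sites, because each site then has its own control group. Here the site is the cluster, and a site-level subgroup has no control group at all. What is left is change from an assessment made shortly after admission. The patients were selected for poor functioning (GAF of 60 or below, plus HoNOS criteria), so that change mixes recovery from the admission episode, regression to the mean and usual care with any effect of the intervention. If centre results were presented as effects, a reader could take them for replication or failure of the intervention when they show neither.

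The diagnosis subgroups raise a different and weaker issue. Finding significance in one diagnosis and not in the other is not evidence that the effects differ, and separate models provide no test of that.

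**Working it through.** **The plan's own figures.** The sample size reproduces. A two-sided 5% test with 80% power for 0.4 SD needs 99.08 patients per arm (t-test), which the protocol takes as 100. The design effect is 1 + (35 − 1) × 0.02 = 1.68, and 200 × 1.68 = 336. Then 336/35 = 9.6, hence 10 centres, and 35/0.7 = 50 recruited per centre gives 500. The main point does not depend on these numbers.

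**Within-centre estimability.** Inputs: 10 centres, allocation by centre, 35 evaluable patients per centre on average (Sample size section).

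- Arm counts within any one centre are 35 against 0, or 0 against 35.
- A model with intercept, baseline and intervention has 3 columns. Within one centre the intervention column is all ones or all zeros, so the matrix has rank 2. This was checked for each of the 10 centres.
- Pooled over the 10 centres, the same matrix has rank 3 of 3.

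The intervention effect is therefore estimable between centres only, and in 0 of 10 centres separately.

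**Precision of the proposed centre-size interaction (illustration).** The protocol does not say how many centres are small or large. Assume 4 and 6, each stratum split evenly between arms, and 35 evaluable patients in every centre. This is a rough simplification, since the strata are defined by size.

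- Variance of a centre mean, in SD² units: 0.02 + 0.98/35 = 0.048.
- Variance of the interaction: 0.048 × (2/2 + 2/3) = 0.080, so SE = 0.283.
- With 10 − 4 = 6 degrees of freedom (t = 2.447), the 95% half-width is 2.447 × 0.283 = 0.69 SD.

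This exceeds the 0.4 SD effect on which the trial is planned.

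**Separate F2x and F3x tests (illustration).** Assume equal diagnostic halves, the same true effect of 0.4 SD in both, ICC 0.02, 17.5 patients per diagnosis per centre and 5 centres per arm, hence 87.5 patients per arm in each half. The 0.4 SD and 0.02 are planning values for EPAS.

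- SE = √[2 × (1 + 16.5 × 0.02)/87.5] = 0.174, and 0.4/0.174 = 2.29.
- Power in each half: 63% (normal), 52% (t with 8 df).
- If the two tests are independent, the chance that exactly one is significant is 2p(1 − p): 2 × 0.631 × 0.369 = 47% (normal) and 2 × 0.523 × 0.477 = 50% (8 df).
- The diagnoses share centres. If the centre effect is fully shared, the covariance of the two estimates is 2 × 0.02/5 = 0.008 and the correlation is 0.008/0.174² = 0.26. Both tests are then significant with probability 0.436 under the normal approximation, so discordance is 2 × (0.631 − 0.436) = 39%. With 8 df, simulation gives about 43%.

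**Precision of the proposed diagnosis interaction (same assumptions).** With fully shared centre effects the centre variance cancels. SE = √(4 × 0.98/87.5) = 0.212, and the 95% half-width is 1.96 × 0.212 = 0.41 SD.

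**The case against.** The best defence is that the by-centre analyses may be purely descriptive. The protocol does not say that they estimate an intervention effect, and in a trial whose background stresses regional differences in psychosocial care, results per site are a natural display. That reading is possible but not stated. The sentence directly follows the one that sends all other outcomes to a model centred on the intervention term. The confounder analyses are labelled exploratory, while the centre subgroups carry no label. The wording therefore needs repair on either reading. If description is meant, saying so is enough.

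It is also fair that nothing confirmatory rests on these analyses, and that misreading of centre results is a risk in reporting and not something the protocol sets out to do.

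On diagnosis, a reader might infer that the F2x and F3x subgroups share the flaw and lack a comparison group. They do not, provided both diagnoses are recruited in both arms. A reader might also infer that the protocol intends to claim a differential effect. It says no such thing, and an interaction test could sit in an analysis plan that is not shown. This part is thus advice on a stated analysis and not an error of the same kind.

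The objections to the discordance figures stand as well. EPAS is not among the outcomes listed for the diagnosis subgroups, so 0.4 SD and ICC 0.02 are borrowed. Independence overstates discordance because centres are shared. The diagnosis mix is not given, and the calculation ignores baseline adjustment, which would raise power.

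**Conclusion.** The main point holds and follows from the design alone: 0 of 10 centres contain both arms, so no within-centre intervention effect can be estimated. The article fixes an analysis that its own randomisation cannot support.

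The secondary point is narrower. The diagnosis subgroups do have a comparison group, on the assumption that both diagnoses are recruited in both arms, but separate models do not test effect modification. The discordance of about 39% (normal approximation, shared centre effects) to 47–50% (independent tests) only illustrates why, under the assumptions listed above. It is not a forecast for the outcomes concerned.

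A reader might go further and conclude that the trial's main result is compromised. The documents do not support that: the primary EPAS comparison is made between randomised centres and does not use the by-centre analyses. Severity is minor to moderate.

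**What to change.** 1. Replace the by-centre subgroup sentence with an intervention-by-centre-size interaction, using the randomisation stratum. State in advance that with 10 centres its precision is low, and report the estimate with its interval.
2. Show centre-level means by arm, labelled as descriptive and not as centre-specific effects.
3. For the outcomes already listed for the F2x and F3x analyses, fit one mixed model with an intervention-by-diagnosis interaction and report its estimate with an interval. Estimates by diagnosis can be shown beside it. This contrast lies largely within centres, so the small number of clusters limits it less.

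The cost is a few sentences of wording. No new data and no change to the sample size or the primary analysis are needed, and the ten by-centre analyses fall away.

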### Eligibility criteria

Inpatients and day hospital patients will be included if they have a severe mental disorder according to the definition of the S3 guideline ‘Psychosocial interventions in severe mental disorders’ (disease duration of ≥ 2 years and substantial impact on activities of daily life) [1]. However, in contrast to the S3 guideline, the inclusion criteria for the present study will be limited to patients with schizophrenia, schizotypal and delusional disorders (ICD-10 F2x) or mood [affective] disorders (ICD-10 F3x) to obtain a more homogenous sample [10]. Considerable consequences on the activities of daily life will be defined as a ‘Global Assessment of Functioning’ (GAF) [11] score ≤ 60 and a ‘Health of the Nation Outcome Scales’ (HoNOS) [12] fulfilling one of two conditions: (a) a score of ≥ 2 on one of the items of the subscale for symptomatic problems (items 6, 7 and 8) and a score of ≥ 2 on each of the four items of the subscale for social problems (items 9, 10, 11 and 12) or (b) a score of ≥ 3 on at least one of these items (9, 10, 11 or 12). Patients of all sexes will be included if they are between the ages of 18 and 65 years. Patients need to have sufficient capacity to understand the research project and to decide about their participation. In case of doubts about the ability to obtain consent of the patient, the responsible physician will decide on the capacity to consent. Legal representatives of patients (if available) will be informed about the study participation in case of consent from the patient.

To include the perspective of relatives of patients with mental disorders, relatives of all sexes will be included if they are aged over 18 years and if they are capable of understanding the research project. Relatives will only be included if they are not in current inpatient or day hospital mental health care.

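### The diagnosis subgroup analyses of the non-primary patient outcomes are planned separately for F2x and F3x, with no stated contrast between diagnoses; a side-by-side reading would be unreliable

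*Protocol article*

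**What the plan says.** In the protocol article, Statistical methods, the primary model for EPAS at six months has "intervention, baseline EPAS-t_0_, centre and centre-size as main regressors with special attention to the intervention (confirmatory"). The other outcomes "will be analysed in a similar way". The diagnosis subgroup plan comes later in the same section: the analyses "will be conducted separately for patients with F2x and F3x diagnoses in additional subgroup analyses". The five groups of outcomes to which this applies are knowledge with attitudes and experiences, use of services, treatment satisfaction, needs, and quality of life.

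EPAS is not in that list. Neither this section nor any other in the article mentions a diagnosis term, an intervention-by-diagnosis term or any other comparison of effects between the diagnoses. The Objectives section poses no question about whether the effect differs by diagnosis. Statistical methods does restrict one set of analyses to exploratory interpretation, but that sentence belongs to the paragraph on possible confounders. The subgroup paragraph has no such label and does not say how the two sets of results will be read.

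**The concern.** Each separate analysis tests whether there is no effect within that diagnosis. Neither tests whether the effect is the same in both. A reader shown an F2x result next to an F3x result will naturally compare them, and the stated plan gives no valid tool for doing so.

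Each analysis compares five centres with five, using only part of the patients, so each has modest power. When two modestly powered tests are run on equal true effects, one will often be significant and the other not. At stake is a spurious message that implementing the patient guideline helps people with affective disorders but not those with psychotic disorders, or the reverse.

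**Working it through.** **Inputs from the article.** Ten centres randomised 1:1 (Randomisation). From Sample size: 35 analysed patients per centre, 70% reached at six months, "We assume a liberal intra-class correlation coefficient of 0.02", and "a medium effect (0.4 SD units) of the implementation intervention on the primary endpoint is expected".

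**Assumptions.** F2x share 30%, 40% or 50%, because the article gives no diagnosis mix; both diagnoses present in every centre; total variance 1, of which 0.02 lies between centres; two-sided 5% level. The 0.4 SD is planned for EPAS only, so 0.2-0.4 SD is used for the listed outcomes.

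**Step 1: the plan's own figure reproduces.** The article states an "error probability of 5% (alpha) and a power of 80% by a t-test for independent samples with a sample size of 2 × 100 participants".
- Per arm: 2 × (1.960 + 0.842)² / 0.4² = 98.1, so 99 (exact t-test 99.1; power 80.4% at 100).
- Design effect: 1 + 34 × 0.02 = 1.68; 200 × 1.68 = 336; 336/35 = 9.6, so 10 centres; 35/0.7 = 50 per centre, 500 in total.

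**Step 2: power within one diagnosis at 0.4 SD.** With share s, n = 175s per arm, m = 35s per centre and SE = √{[1 + (m − 1) × 0.02] × 2/n}.
- s = 0.5: SE = √(1.33 × 2/87.5) = 0.174; power 63% (normal) or 52% (t on centre means, 8 df).
- s = 0.3: SE = √(1.19 × 2/52.5) = 0.213; power 47% or 38%.
- s = 0.7: SE = √(1.47 × 2/122.5) = 0.155; power 73% or 62%.

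**Step 3: how often exactly one diagnosis is significant when the effects are equal.** Simulation with 40,000 trials per scenario, a centre effect shared by both diagnoses, and t-tests on centre means (8 df). F2x/F3x patients per centre were 18/17, 14/21 and 10/25.

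| True effect in both | F2x 50% | F2x 40% | F2x 30% |
|---|---|---|---|
| 0 | 9% | 9% | 9% |
| 0.2 SD | 26% | 26% | 26% |
| 0.3 SD | 39% | 38% | 40% |
| 0.4 SD | 43% | 44% | 48% |

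An interaction test on the within-centre F2x-F3x differences rejects in about 5% in every cell. These rates are per outcome.

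**Step 4: sensitivity to baseline adjustment.** The plan adjusts for baseline and Step 3 does not. If baseline explains half the residual variance (assumption: 0.98 becomes 0.49), the discordance is 30-31% at 0.2 SD, 39-42% at 0.3 SD and 32-39% at 0.4 SD. It falls at 0.4 SD because both tests gain power, and rises at 0.2 SD for the same reason.

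**Step 5: which interaction test is safe.** If centre effects differ by diagnosis (extra variance 0.01-0.02 for each diagnosis, assumption), a model with a single random centre effect and patient-level degrees of freedom (330) rejects falsely in about 7-9%. The test on within-centre differences with 8 df stays at 5%.

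**Step 6: precision of the interaction.** With a shared centre effect, SE = √{0.98 × 2/(175s) + 0.98 × 2/[175(1 − s)]} = 0.212 (s = 0.5) or 0.231 (s = 0.3).
- With normal quantiles, power for 0 versus 0.4 SD is 47% or 41%, and the difference detectable with 80% power is 0.59 or 0.65 SD.
- With 8 df (t = 2.306), the 95% CI half-width is 2.306 × 0.212 = 0.49 SD or 2.306 × 0.231 = 0.53 SD, and power falls to about 38% or 33%.

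**The case against.** The strongest reply is that the article commits to no faulty inference. It announces additional analyses in two diagnostic groups and stops there. Effects estimated within each diagnosis, with intervals, are a legitimate description, and no objective asks about effect modification. A reader might infer that the authors intend to claim a difference between diagnoses whenever one p-value falls below 5% and the other does not. The text does not support that: it sets no significance rule for the subgroups and promises no comparison. Nor can one infer that no interaction test will ever be run. The article condenses a fuller protocol, an analysis plan may exist, and separate analyses do not exclude an added contrast.

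The figures can also be challenged. The 0.4 SD belongs to EPAS, the diagnosis mix is assumed, and tests on centre means are not the planned baseline-adjusted models. With no effect at all, discordance is only about 9%.

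These replies limit the point but do not remove it. The article does choose a method, separate analyses, and that method alone cannot show whether the effects differ. Baseline adjustment changes the size of the problem but leaves discordance at 30% or more for a true effect of 0.2-0.4 SD. Low power of the interaction is a reason to report an interval, not to omit the contrast.

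**Conclusion.** The point holds in a limited form. As stated, the plan yields two within-diagnosis results and no estimate of the difference between them. Under equal true effects of 0.2-0.4 SD, a pattern of one significant and one non-significant diagnosis would occur in about 26-48% of trials per outcome, or about 30-42% if baseline explains half the residual variance, against about 5% false differences from an interaction test.

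This rests on 35 analysed patients in each of 10 centres, ICC 0.02, an F2x share of 30-50% and an effect size borrowed from a different outcome, so the range matters more than any single figure. The analyses are additional and concern non-primary outcomes, and the confirmatory EPAS test is untouched. This is a minor, inexpensive improvement, not a flaw in the trial's main conclusion.

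**What to change.** For each listed outcome, fit one mixed model in all patients with:
- intervention, diagnosis group (F2x or F3x) and intervention × diagnosis;
- the baseline value, where one is measured, and centre size;
- a random centre effect and a random centre-by-diagnosis effect, with cluster-level degrees of freedom for the interaction. Testing the within-centre F2x-F3x differences between arms on about 8 df is equivalent in purpose.

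Report the interaction estimate with its 95% CI as the subgroup result, labelled exploratory. Give the F2x and F3x effects with CIs from the same model as description. State that no conclusion will be drawn from significance in one diagnosis only.

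The cost is a few sentences of analysis wording, and no new data are needed. The drawback is low power: with a half-width near 0.5 SD before any gain from baseline adjustment, the usual result will be no clear evidence of a difference, with a wide interval. If the analysis plan already contains this contrast, a cross-reference is enough.
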